## Abstract

**Background:**

Current NHS policy encourages an integrated approach to provision of mental and physical care for individuals with long term mental health problems. The ‘PARTNERS2’ complex intervention is designed to support individuals with psychosis in a primary care setting.

**Aim:**

The trial will evaluate the clinical and cost-effectiveness of the PARTNERS2 intervention.

**Design & setting:**

This is a cluster randomised controlled superiority trial comparing collaborative care (PARTNERS2) with usual care, with an internal pilot to assess feasibility. The setting will be primary care within four trial recruitment areas: Birmingham & Solihull, Cornwall, Plymouth, and Somerset. GP practices are randomised 1:1 to either (a) the PARTNERS2 intervention plus modified standard care (‘intervention’); or (b) standard care only (‘control’).

**Method:**

PARTNERS2 is a flexible, general practice-based, person-centred, coaching-based intervention aimed at addressing mental health, physical health, and social care needs. Two hundred eligible individuals from 39 GP practices are taking part. They were recruited through identification from secondary and primary care databases. The primary hypothesis is quality of life (QOL). Secondary outcomes include: mental wellbeing, time use, recovery, and process of physical care. A process evaluation will assess fidelity of intervention delivery, test hypothesised mechanisms of action, and look for unintended consequences. An economic evaluation will estimate its cost-effectiveness. Intervention delivery and follow-up have been modified during the COVID-19 pandemic.

**Conclusion:**

The overarching aim is to establish the clinical and cost-effectiveness of the model for adults with a diagnosis of schizophrenia, bipolar, or other types of psychoses.

## How this fits in

The current NHS Community Mental Health Transformation policy (NHS England 2019) aims to ensure all those with psychosis and a need for care are supported, and for much of this to be carried out as a collaboration between primary care and third sector organisations. Previously, the policy focus was specialist mental health care via community teams and then discharge to primary care for those with less, but often still significant, need, thus presenting a significant divide between primary and secondary care. The authors have completed 2.5 years of preparatory work to understand the nature, strengths, and limitations of the current status of primary–secondary care collaboration and, alongside service users, have developed and piloted a primary care-based collaborative care model. PARTNERS2 is the first trial of that model to be carried out in the UK.

## Introduction

This article presents the protocol (version 7.3, 18.08.2020) for the PARTNERS2 (develoPing intergrAted primaRy care for paTieNts with sERiouS mental illness) cluster randomised controlled trial (RCT) to assess the clinical and cost-effectiveness of a primary care-based collaborative care model for people with diagnoses of schizophrenia, bipolar, or other psychoses. Such individuals are recognised as having considerable unmet physical, emotional, and social needs.^1^ The current NHS Community Mental Health Transformation policy (NHS England 2019) aimed to ensure all those with psychosis and a need for care are supported, and for much of this to be carried out as a collaboration between primary care and third sector organisations. Previously, the policy focus was specialist mental health care via community teams and then discharge to primary care for those with less, but often still significant, need, thus presenting a significant divide between primary and secondary care.

PARTNERS1, which ran during this previous policy, found that nearly a third of people in the UK with a diagnosis of schizophrenia, bipolar, or other psychoses were seen only in primary care.^1^ Poor continuity of care and lack of information exchange between primary and secondary care created barriers to effective support. To overcome these challenges, the PARTNERS model was developed to improve collaboration between secondary care, primary care, and the service user.

### Feasibility and piloting in the PARTNERS2 programme

Initial phases of PARTNERS2 focused on understanding current care pathways, developing the intervention, and addressing trial science questions. Different phases and timescales of the overall programme are summarised in Table 1. This protocol was written during the delivery and follow-up phase of the trial; use of past and present tense in the paper indicate activities at the time of writing.

**Table 1. table1:** Programme and trial phases and timelines

**Stage and key aims**	**Duration**	**Key dates**
**Develop** **f** **easibility stage**Aims:To develop and refine the intervention modelTo agree outcome measuresTo test recruitment processes	24 months	2014–2016
**Randomised controlled trial** **: internal pilot**Aims:To further test feasibility of both recruitment and the intervention delivery for patients and GP practices.To assess recruitment against objectives: GP practice recruitment rates – 8 GP practices per site (24 total) Participant eligibility rates – 24 participants per site (72 total) To assess delivery and safety of intervention—for example, intervention delivery (care partners in place) and adverse events such as crisis care (home treatment teams), and admissions (psychiatric).To review initial sample size target of 336 participants	6 months	Trial started: 1/10/2017Trial registered: 16/10/2017First participant recruited: 8/6/2018
**R** **CT** **(completion of RCT following internal pilot):**Aim:To establish the clinical and cost-effectiveness of primary care based collaborative care for people with a clinical diagnosis of schizophrenia, bipolar, or other types of psychosis^a^	Completion of recruitmentFollow up: 10–12 months	Recruitment end date: 28/2/2020Follow up end: 28/12/2020Data collection end date:31/3/2020Study end date: 30/04/2021

a Revised recruitment target of 204 participants with a diagnosis of schizophrenia, bipolar, or other types of psychosis from ~34 clusters (GP practices), based on prespecified sample size recalculation (December 2019) and funder requirements (January 2020).

RCT Randomised controlled trial

A multi-site notes review was carried out to understand the relationship between primary and secondary care. The intervention was co-produced by clinical academics, researchers, and people with lived experience of ongoing mental health needs. The latter group were engaged through three Lived Experience Advisory Panels (LEAPs) advising the programme. The intervention was founded on Wagner’s Chronic Care Model,^2^ principles of personal recovery,^3^ and coaching for mental health.^4^ The programme theory and practice were iteratively developed utilising a realist approach,^5,6^ wider literature, primary data, and stakeholder input.^7^ The intervention was ‘fixed’ after the refinement in this feasibility stage.^8^

Approaches to recruitment were tested iteratively involving flexibility for non-responders and support from NHS employed researchers for pre-consent work (initial identification and approach by letter and telephone) in primary care. A core outcome set for use in bipolar disorder trials was developed.^9^ To account for the wider psychosis target population in PARTNERS2 and the nature of the intervention, an additional stakeholder consultation was undertaken to select outcomes and measures. QoL was selected as the most important outcome domain. Relevant measures of QoL were reviewed and the Manchester Short Assessment Quality of Life (MANSA) was selected on the basis of being clinically relevant to the target population and as potentially amenable to change by the intervention. The MANSA has good validity and reasonable internal consistency.^10^

### Challenges during trial set up, internal pilot, and COVID-19

Health Research Authority guidance changed while planning the trial, which meant that the flexible approaches developed during the conduct of the pilot phase were initially not permitted due to confidentiality concerns. Some components (for example, practices supported in pre-consent identification and approaches by NHS-employed researchers) were reinstated following Health Research Authority amendments once recruitment was shown to be slow. Changing circumstances in host NHS Trusts and delays in trial set-up led to withdrawals from the study of one trust during set-up, and the Lancashire Care Foundation Trust during the early phase of recruitment, resulting in the need to identify new host trusts. Although not all recruitment targets had been met, recruitment in two trusts (Cornwall and Plymouth) had been shown to be successful, and thus the trial was continued pending a delayed sample size review carried out in late 2019. As detailed in Table 1, this review led, in December 2019, to the recommendation from the trial oversight groups (Data Monitoring Committee [DMC] and Trial Steering Committee [TSC]) for a reduction of the original sample size. In January 2020, the funder requested recruitment to stop in order to complete the trial within the funding envelope and with a change in power (see sample size section below).

Soon after recruitment had closed, and partway through intervention delivery and follow-up data collection, the COVID-19 pandemic and national lockdown in the UK (March 2020) had a sudden impact on the trial. In consultation with the TSC and funder, the research team adapted methods for intervention delivery, follow-up data collection, and the ongoing process evaluation. These adjustments are outlined in Table 2. The adapted methods were tested for an 8-week period. In light of the success of this adaption, the continued uncertainty surrounding the pandemic, and risk assessments for both service users and practitioners, the decision was made to continue remote delivery, where possible, of both the intervention and follow-up, and process evaluation data collection until the end of the trial. Face-to-face delivery and data collection were used when safe and preferred by participants.

**Table 2. table2:** Adjustments to the trial due to COVID-19 restrictions (8-week trial phase)

**Challenges**	**Solutions**
Adapting the intervention to remote delivery	Delivery via telephone or video conferencing software. Intervention practitioners received training on using video conferencing software and delivering interventions remotely. Coaching and goal-setting were adjusted to be appropriate to a lockdown environment. The majority of participants found it acceptable to continue the intervention after adaption to remote delivery. Practitioners delivering the intervention reported they were able to continue collaborating with primary care by remote means.
Collecting data remotely	Follow-up data and process evaluation data collected via telephone, video conferencing, or post. For the secondary outcome of time use, data collection was adjusted to include activities participants conducted remotely, such as attending church via video conferencing.
Understanding the feasibility and acceptability of continuing the intervention and data collection remotely. This included acceptability to participants and the feasibility of collaborating with primary care.	8-week trial phase, including rapid realist evaluation. This realist evaluation considered: the experiences of the intervention practitioners delivering the intervention during COVID-19 restrictions; and during routine audio-assisted recall interviews with service users, exploring their experiences of engaging with the intervention by remote methods.

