### Outcome measures

The trial primary outcome is QOL at the primary endpoint, as measured by the MANSA. This is a self-complete questionnaire comprising both objective and subjective questions across different life domains (work and education, personal finances, leisure activities, social life, living situation, family life, personal safety, and health). Objective items (for example, employment status) are described separately and not aggregated. Satisfaction is rated on a 7-point Likert scale (1 = negative extreme, 7 = positive extreme) and scorings are processed to provide three different types of results: separate domain ratings; an overall MANSA score, assessing QOL (the primary outcome); and a general (single item) QOL rating. Staff undertaking data collection were trained in using the measure. The MANSA was collected at baseline and follow-up.

Secondary outcome measures were assessed at baseline and follow-up (listed in Table 4). Data collection forms are available from the authors on request.

**Table 4. table4:** Schedule of assessment for practices and participants

**Activity**	**Pre-baseline**	**Baseline**	**Pilot phase** **6** months	**Month 10** **±30** **days**
Eligibility check	*x*			
Valid informed consent	*x*	*x*		*x*

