### Data management and statistical analysis

Processes to ensure the accuracy of the data are detailed in the trial data management plan. Coding and validation have been agreed between the trial team, statistician, and the trial programmer.

Data from case report forms are entered onto the database by researchers and/or CTU staff in accordance with working instructions, and data queries are managed through the use of data clarification forms. Corrections which are self-evident will be agreed with the Chief Investigator (CI).

Statistical analyses are pre-specified and a detailed statistical analysis plan will be agreed by the DMC and signed off by the independent TSC statistician prior to locking of the database. This plan will be available from the authors on request. Results will be reported in line with relevant Consolidated Standards of Reporting Trials (CONSORT) guidelines.^14–16^ The primary analyses will be undertaken according to a modified intention-to-treat principle, including all participants who are randomised and who provide valid outcome data at baseline and 10-month follow-up. For the primary outcome, multiple imputation will be undertaken in order to present a sensitivity analysis of the full intention-to-treat population.

The primary analysis of the primary outcome will be undertaken blinded to allocated group, and will involve comparison of the change in overall MANSA score between baseline assessment and 10-month follow-up between allocated groups. The comparison will be undertaken using a mixed-effects linear regression model adjusted for baseline MANSA score, as well as the stratification factors (region and practice size), and including a random effect term for GP practice to account for the hierarchical structure of the data induced by the cluster randomisation. Results without adjustment for the stratification variables will also be presented. Model assumptions will be checked and appropriate data transformations sought if required. Continuous secondary outcomes will be analysed similarly. All treatment effect estimates will be presented alongside 95% CIs. Additional secondary analyses of the primary outcome will be considered to explore the effect of intervention fidelity and Care Partner availability on the estimated treatment effect, using Complier Average Causal Effect and per-protocol analyses.

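### Time-use collection was widened when lockdown fell mid-follow-up, but the stated model for continuous secondary outcomes has no period term: no bias, but an avoidable and unquantified loss of precision

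*Protocol article*

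**What the plan says.** The protocol article (version 7.3, dated 18.08.2020 in the Introduction) was written after the pandemic changes. Table 1 dates the first participant to 8/6/2018, the end of recruitment to 28/2/2020 and the end of follow-up to 28/12/2020. The section on challenges during set-up, internal pilot and COVID-19 says that "partway through intervention delivery and follow-up data collection, the COVID-19 pandemic and national lockdown in the UK (March 2020) had a sudden impact".

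Table 2 then lists two changes to follow-up. On mode: "Follow-up data and process evaluation data collected via telephone, video conferencing, or post". On content: "For the secondary outcome of time use, data collection was adjusted to include activities participants conducted remotely, such as attending church via video conferencing". The text before the table adds "Face-to-face delivery and data collection were used when safe and preferred by participants", so mode was mixed after lockdown rather than wholly remote.

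The section on data management and statistical analysis fixes the primary analysis as a "mixed-effects linear regression model adjusted for baseline MANSA score, as well as the stratification factors (region and practice size"), with a random effect for GP practice. For the other continuous outcomes it says only: "Continuous secondary outcomes will be analysed similarly". The further analyses it names are one without the stratification variables, multiple imputation, complier average causal effect and per-protocol. None deals with period or mode of follow-up.

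**The concern.** Hours per week in structured activity is the first secondary hypothesis listed under Objectives. Lockdown can move it in two ways: the restrictions change what people do, and the wider collection changes what is counted. For anyone followed up after lockdown, baseline was recorded under the earlier content and follow-up under the wider one, so the baseline covariate cannot remove the shift.

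Allocation was withheld until recruitment in a practice was complete. Recruitment by practice suggests that baseline dates, and so the follow-ups 10 months later, tend to bunch by practice. A shift between periods would then act largely as extra between-practice variance, which is the costly kind in a cluster trial. At stake is the precision of the time-use comparison. For MANSA the same argument applies to mode and circumstances of follow-up, but the content of the measure is not reported to have changed.

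**Working it through.** **Inputs from the article** (Sample size; Abstract): target difference 0.45; SD 0.9; ICC 0.05; coefficient of variation of cluster size 0.74; baseline to follow-up correlation 0.5; dropout 20% of individuals and 10% of clusters, so retention 0.8 × 0.9 = 0.72; planned 204 participants in about 34 practices; achieved 200 in 39.

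**Assumptions:** two-sided 5% level (read from the 95% CIs); size of the period shift; share p of practices followed up after lockdown. The 39 participants with complete data at the late-2019 review cap the post-lockdown share at about 80% of 200. Even recruitment from 8/6/2018 to 28/2/2020 (630 days), with baselines after about late May 2019 (281 days) falling due after lockdown, would give 281/630 = 45%. The range p = 0.5 to 0.8 is used; p = 0.45 gives almost the same result as 0.5.

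**Step 1. Reproduce the stated power.** Variance after baseline adjustment: 0.81 × (1 − 0.5²) = 0.6075. Design effect at m = 6: 1 + ((0.74² + 1) × 6 − 1) × 0.05 = 1.414. Analysed n = 204 × 0.72 = 146.9. SE = √(4 × 0.6075 × 1.414 / 146.9) = 0.153. Noncentral t with 34 × 0.9 − 2 = 28.6 df gives power 0.811, against a stated 80%. It reproduces.

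**Step 2. Achieved sample, no shift.** m = 200/39 = 5.13, design effect 1.347, n = 144, SE = 0.151, power 0.826.

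**Step 3. Add a shift wholly between practices.** Added variance = p(1 − p) × shift². At 0.5 SD (0.45 points) and p = 0.5 this is 0.25 × 0.2025 = 0.0506. The between-practice part rises from 0.05 × 0.6075 = 0.0304 to 0.0810, the total to 0.6581, the ICC to 0.123, the design effect to 1.854 and the SE to 0.184. Power is 0.660.

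| Shift | ICC (p = 0.5 to 0.8) | Power, no period term | Loss from 0.826 |
|---|---|---|---|
| 0.1 SD | 0.053 to 0.052 | 0.818 to 0.821 | 1 point or less |
| 0.25 SD | 0.069 to 0.062 | 0.781 to 0.797 | 3 to 5 points |
| 0.5 SD | 0.123 to 0.098 | 0.660 to 0.715 | 11 to 17 points |

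**Step 4. If the shift is not between practices.** Wholly within practices, a 0.5 SD shift gives 0.803 to 0.811, a loss of about 2 points. In a simulation (30 practices, 800 runs per setting), a 0.5 SD shift mixed half within practices gave 0.78 against 0.83 with no shift.

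**Step 5. Bias and type I error.** In the same simulation, without the period term, the mean estimate was 0.44 to 0.46 against a true 0.45. Type I error was 0.055 at a 0.5 SD shift and 0.040 at 1 SD.

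**Step 6. What the term recovers and costs.** With the term, simulated power was 0.79 to 0.82 whatever the shift. A second simulation (39 practices, 200 participants, 28% loss, p = 0.6, 1,500 runs per row, Monte Carlo SE about 1 point) gave, without versus with the term: 0.5 SD, 68% v 75%; 0.33 SD, 75% v 77%; 0.22 SD, 76% v 76%; no shift, 80% v 78%. By formula the lost degree of freedom alone costs 0.1 point; chance imbalance of period between arms makes up most of the rest.

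**The case against.** The strongest objection is that this belongs to the statistical analysis plan, which is announced but not shown and may already contain a period term or a COVID-19 sensitivity analysis. That stands as a limit: the point concerns the model as stated here. It does not dispose of the point, because an article dated after the changes names the covariates and applies the model to the continuous secondary outcomes.

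Next, the stated model is valid, and the gain depends on assumptions. This also stands. Below a shift of about 0.2 SD the term gains little or nothing. The loss is substantial only for a shift near 0.5 SD lying mostly between practices. The article does not say how long each practice recruited, follow-up has a ±30-day window, and the region term may absorb part of the timing if regions recruited at different times. Counting remote activities may also offset hours lost to lockdown, so the two effects may oppose each other.

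Third, the figures use MANSA parameters. The article gives no SD, ICC, target or power for time use, so they only illustrate the standardised scale.

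A reader might infer that the change biases the comparison between arms, or that the outcome was replaced. The documents support neither: the reported change affects what was counted, with no difference between arms described, and allocation stayed concealed until a practice had finished recruiting.

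**Conclusion.** The point holds as a matter of precision for time use. Lockdown divides the follow-ups, the activities counted were widened, and the stated model leaves any resulting shift in the residual, probably mostly at practice level. The loss runs from about 1 point of power or less (0.1 SD) through 3 to 5 points (0.25 SD) to 11 to 17 points (0.5 SD). It rests on MANSA planning values, an assumed post-lockdown share of 50% to 80%, and a shift wholly between practices; it is smaller if practices straddle March 2020 or region absorbs the timing.

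It might be inferred that the trial has lost a known amount of power on its primary outcome, or that the MANSA model must change. The article gives neither the shift nor the split, and reports no change in MANSA content, so that does not follow. Nor does a period main effect answer whether the intervention works differently when delivered remotely. With a main-effect SE of about 0.16 and a 60/40 split, the interaction SE is 0.16 × √(1/0.24) = 0.33, so power is only about 28% even for an interaction of 0.45.

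**What to change.** Before database lock, in the statistical analysis plan:

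- **Time use:** add a fixed effect for whether the scheduled follow-up date (baseline date plus 10 months) falls before or after the March 2020 lockdown. Use the scheduled date, not the actual one, because treatment cannot affect it.
- **Time-use content:** where remote activities were recorded separably, report a sensitivity analysis that excludes them, so that the original content is also analysed. If they were not separable, say so.
- **MANSA:** keep the stated primary model. Add the same period term as a sensitivity analysis only, and show any arm-by-period estimate descriptively with its CI, without a test on which conclusions depend.

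The cost is wording, about 1 degree of freedom in the time-use model, and up to about 2 points of power if there turns out to be no shift. No new data are needed beyond the baseline date and the existing time-use records.
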